### Outcomes

#### Primary outcome

##### Number of exacerbations

The primary outcome is the number of respiratory system exacerbations occurring during the treatment period. A respiratory system exacerbation is defined in this trial as either respiratory tract symptoms leading to start of systemic antibiotic treatment, irrespective of results of bacterial culture, or as a decline in FEV_1_% predicted equal to or above 10 percentage points relative to the average of FEV_1_% predicted at screening and randomization, whether or not antibiotics are prescribed.

The occurrence of exacerbations will be assessed by patient interview, physical examination and spirometry. At each trial visit, and at any extra contacts with the trial sites attributable to exacerbations, the participants will be interviewed regarding symptoms and concomitant medication since last contact with the trial site. The interview will be supplemented by a weekly patient diary on symptoms and antibiotics. A physical examination reviewing the participants’ general condition, vital signs, ears, heart and lungs will be performed at all visits.

### Secondary outcomes

#### Lung function measured by spirometry

Spirometry will be performed according to the American Thoracic Society/European Respiratory Society (ATS/ERS) criteria [25] at each visit. The outcomes from spirometry are FEV_1_, forced vital capacity (FVC) and forced expiratory flow at 25–75 % of FVC with results expressed in percentage of predicted [26]. Short and long acting bronchodilators and anticholinergics will be withheld 6 and 12 h prior to spirometry, respectively.

#### Static lung volumes & airways resistance

Measurement of residual volume (RV)% predicted, RV/total lung capacity (TLC)% predicted and airway resistance (Raw)% predicted by body plethysmography will be performed at all trial visits during the 6 month treatment period using a standardised whole-body plethysmograph and according to ATS/ERS recommendations [27].

#### Ventilation distribution inhomogeneity

Assessment of ventilation distribution inhomogeneity by nitrogen multiple breath washout (N_2_ MBW) will be performed at all the trial visits during the treatment period. The outcomes derived from N_2_MBW will be lung clearance index (LCI), which is a measurement of overall ventilation inhomogeneity in the lungs, and the indexes S_acin_xV_T_ and S_cond_xV_T_ reflecting ventilation inhomogeneity in the small conducting and acinar airways, respectively. N_2_ MBW will be measured according to ERS/ATS Consensus Statement for inert gas washout measurement [28] and will be performed prior to spirometry. All trial sites will use the instrument EXHALYZER®D (ECO MEDICS AG, Duernten, Switzerland) to perform N_2_ MBW, and results of the N_2_ MBW will be analysed using the software ‘Spiroware’ (ECO MEDICS AG, Duernten, Switzerland).

#### Health-related quality of life

Newly developed, PCD-specific health-related quality of life questionnaires (QOL-PCD) will be used to assess patient-reported outcomes [23]. The QOL-PCD has age-appropriate versions available for children 6–12 years, adolescents 13–17 years, adults, and a parent proxy. The following domains on the QOL-PCD will be used as outcome measures: Respiratory Symptoms, Sinus Symptoms, and Ears and Hearing. The QOL-PCD is available in the primary languages of the participating countries (English, Danish, Dutch, German and Swiss German), and an electronic speaking questionnaire is available for the youngest age group. The QOL-PCD will be completed at all visits, at extra contacts with trial sites attributable to exacerbations, and will be administered prior to any other study procedures to reduce bias.

#### Hearing impairment

Audiometry and tympanometry will be performed at randomization and at the end of the treatment period at local hospital departments of otorhinolaryngology. Hearing thresholds will be determined as the pure tone average at 0.5, 1, 2, 4 & 8 kHz measured by air conduction and as discrimination loss. Bone conduction thresholds will only be measured if air conduction thresholds are above 10 dB.

#### Sputum microbiology

Sputum will be sampled at all visits for culture of bacteria and fungi. When the participant cannot cough up sputum voluntarily, then sampling of sputum is performed according to local procedures e.g. by use of cough swabs or by laryngeal suction. Sputum will be cultured for at least the following microorganisms: *Streptococcus pneumonia*, *Group A beta-haemolytic Streptococcus*, *Staphylococcus aureus*, *Moraxella catharrhalis*, *Haemophilus influenzae*, *Pseudomonas aeruginosa*, *Burkholderia cepacia complex*, *Achromobacter xylosoxidans* and *Aspergillus fumigatus*. Microscopy of bacteria will not be performed. During an exacerbation, participants will be asked to deliver sputum samples, which, in addition to regular cultures, will be analysed for respiratory viruses and mycoplasma pneumoniae by polymerase chain reaction. The testing will include the following viruses: Influenza A and B, rhino virus, adenovirus, respiratory syncytial virus, bocavirus, enterovirus, metapneumovirus and parainfluenza virus. Culture incl. antibiotic susceptibility testing and polymerase chain reaction are performed at the local microbiological laboratories.

#### Inflammatory markers

In those participants who can expectorate sputum and in participants where laryngeal suction is performed, a sample of sputum from randomization and from the end of the treatment period will be stored in a biobank for later analysis of cytokines and neutrophil elastase. Blood samples will be taken at simultaneous time points for measurement of C-reactive protein, white cell count including differential cell counts and cytokines. C-reactive protein and white cell count including differential counts will be analysed in the local hospital laboratories. The blood samples for measurement of cytokines will be centrifuged at the local hospital laboratories to isolate the serum, and the serum will be kept in a biobank for later analysis. After the end of the trial, all the serum samples and sputum samples will be analysed for cytokines and neutrophil elastase collectively at the Department of Clinical Microbiology at Rigshospitalet in Denmark.

#### Adverse events

Participants will be assessed for the occurrence of adverse events using the following measures: Interview regarding any new or worsening of symptoms; physical examination including vital signs; microbiological analysis of sputum and antibiotic susceptibility testing; audiometry; and blood samples to monitor bone marrow, liver and kidney function. Interview, physical examination, and culture of sputum and antibiotic susceptibility testing will be performed at all visits, whereas audiometry and blood sampling will only be performed at randomization and at the end of the treatment period. At screening and end of the treatment period, sputum will be tested for non-tuberculous mycobacteria [29, 30]. The antibiotic susceptibility testing will at least include susceptibility of bacteria to azithromycin and either amoxicillin with clavulanic acid or penicillin (depending on the bacterial species). The blood samples will include determination of haemoglobin, white cell count, thrombocytes, alanine transaminase and creatinine and will be analysed in the local hospital laboratories.

An independent data and safety monitoring board will monitor patient safety and treatment efficacy data while the trial in ongoing.

### Sample size

The planned number of participants to be enrolled in the trial is 125. The sample size is calculated based on the primary endpoint and has been estimated based upon detecting a 50 % reduction in number of exacerbations (assuming a mean of 2.5 exacerbations per year in the placebo group) in the azithromycin group with a statistical power of 90 % and assuming Poisson distribution. On this basis, a sample size of 100 participants completing the trial will be required, with 50 participants in each treatment arm. Allowing for a dropout rate of 20 %, the total number of participants to be enrolled in the trial is 125. Power is 70 % to detect a difference of 5 percentage points between treatments in the pre- to post-intervention change in FEV_1_ % predicted (assuming a SD of 10 % for intra-subject change); and power is 88 % to detect a difference of 5 percentage points in the pre- to post-intervention change in LCI (assuming a SD of 8 % for intra-subject change). Calculations of power are based on two-sided testing with an alpha level of 0.05.

### Statistical analysis

Two analysis populations are defined: Intention-to-treat population and per-protocol population. All participants who are randomized will be included in the intention-to-treat population analysis, and all available data from drop-outs will be included in this intention-to-treat analysis. The per-protocol population analysis will include all participants, who are randomized, have completed the trial, have not been discontinued from treatment, and have had no major protocol deviations. A participant will be considered to have completed the trial if he or she has completed all the five visits. The per-protocol population will be determined prior to unblinding.

Data will be summarized descriptively. For continuous variables, descriptive statistics such as mean and SD, or median and range (depending on normality) will be summarised. For categorical variables, the frequency will be presented. Analysis of the primary and secondary outcomes will be based on the intention-to-treat population and will be repeated based on the per-protocol population. The primary outcome will be analysed using Poisson regression, with adjustment for age as a potential confounder. The continuous secondary outcomes will be modelled using a linear mixed model including a fixed time-specific treatment effect and random effects of trial site and person. Additional potential confounders, such as age, can be adjusted by including them in the linear mixed model as fixed main effects. The categorical secondary outcomes will be analysed by McNemar’s test or test of marginal homogeneity, as appropriate. All statistical inference tests will be performed using two-sided testing with a significance level (alpha) of 0.05. No adjustment will be made to the significance level for the multiple statistical comparisons planned as part of the secondary analyses.

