### Intervention

The intervention is oral tablets of azithromycin or identical tablets of placebo administered three times a week (Monday-Wednesday-Friday) for 6 months. The dose of azithromycin is 250 mg for participants with a body weight below 40 kg at screening and 500 mg for participants weighting 40 kg or above, corresponding to a weekly dose of 750 mg or 1500 mg azithromycin, respectively.

Systemic or inhaled antibiotic treatment, besides the potential azithromycin maintenance therapy during the trial, is only allowed if needed during clinical exacerbations and in the case of new infection with *Pseudomonas aeruginosa*, *Achromobacter xylosoxidans* or *Burkholderia complex*. Treatment of respiratory system exacerbations, if culture and antibiotic susceptibility is not yet known, will be 14 days of oral amoxicillin with clavulanic acid as first-line treatment and clarithromycin as second choice. More severe exacerbations will be treated according to local guidelines. Treatment of first time or intermittent colonization with *Pseudomonas aeruginosa* will be inhalation of colistin in combination with oral ciprofloxacin or inhalation of Tobramycin for 3-4 weeks. In case of treatment failure, early relapse or signs of development of chronic *Pseudomonas aeruginosa* infection, antibiotic treatment will be intensified to last for 3 months. Treatment with the trial medication will continue throughout the trial simultaneously with any antibiotics prescribed for exacerbations or infection with *Pseudomonas aeruginosa*. Any other pre-trial medication will continue unchanged, and any other new prescriptions, which are considered necessary for the participant’s welfare, may be given.

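### The primary Poisson regression has no stated allowance for extra-Poisson variation: with default standard errors and unexplained differences between patients the type I error exceeds 5%, and the 90% power is sensitive to the same assumption

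*Protocol article*

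**What the plan says.** The endpoint is a count per person: "The primary outcome is the number of respiratory system exacerbations occurring during the treatment period" (Protocol article, Number of exacerbations). Treatment is "administered three times a week (Monday-Wednesday-Friday) for 6 months" (Intervention).

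The Statistical analysis section gives the primary model in one sentence: "The primary outcome will be analysed using Poisson regression, with adjustment for age as a potential confounder". It mentions no dispersion parameter, robust or scaled variance, negative binomial model or site effect for this outcome. The same paragraph does give random effects of site and person, but only for the continuous secondary outcomes.

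The Sample size section rests on the same distribution. It aims at "detecting a 50 % reduction in number of exacerbations", "assuming a mean of 2.5 exacerbations per year in the placebo group", "with a statistical power of 90 % and assuming Poisson distribution". This leads to 50 completers per arm and, with 20% dropout, 125 enrolled. It adds: "Calculations of power are based on two-sided testing with an alpha level of 0.05".

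**The concern.** A Poisson model sets the variance of each person's count equal to its mean. That holds if all participants of the same age and arm share one underlying exacerbation rate and events occur independently. If rates differ between such participants, counts vary more than the model allows, and standard errors taken from the model are too small.

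The article gives reasons to expect such differences. The Discussion names the wide age range and between-site differences in routine management as challenges of the study. The Eligibility section admits any FEV1 above 40% predicted and sets a minimum of 30 antibiotic days in two years with no maximum. Adjusting for age removes only the part of the variation that age explains.

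This is the trial's one primary test. If its standard error is too small, the interval for the rate ratio is too narrow and the two-sided 5% level is not kept. The power calculation makes the same assumption, so it gives no margin.

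**Working it through.** **Inputs from the Protocol article.** Placebo rate 2.5 per year, so 1.25 events in 6 months; a 50% reduction gives 0.625; 50 completers per arm; two-sided alpha 0.05 (Sample size, Intervention).

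**Input not in the article.** The dispersion k in variance = mu + k·mu². The values below are assumptions.

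**Step 1: reproduce the stated power (k = 0).**
- Log rate ratio: variance = (1/1.25 + 1/0.625)/50 = 2.4/50 = 0.048, SE = 0.2191. Power = Phi(0.6931/0.2191 − 1.960) = 88.6%.
- Rate difference: SE = sqrt(1.875/50) = 0.1936. Power = Phi(0.625/0.1936 − 1.960) = 89.8%.
- Square-root transform: 2(1.1180 − 0.7906)/sqrt(2/50) = 3.275. Power = Phi(3.275 − 1.960) = 90.6%.
- Enrolment: 100/0.8 = 125.

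The stated 90% and 125 both reproduce.

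**Step 2: what k means.** Suppose half the participants have 1.25 exacerbations a year and half have 3.75. The mean is 2.5 and k = 1.25²/2.5² = 0.25. The low end of the range is thus a moderate spread.

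**Step 3: type I error with model-based Poisson standard errors.** With both arms at mean mu, the true variance of the log rate ratio is (1 + k·mu) times the reported one. The actual level is therefore 2·Phi(−1.960/sqrt(1 + k·mu)).

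**Step 4: power of a test whose standard error is correct.** The variance is (2.4 + 2k)/n, with n = 50 per arm.

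| k | 1 + 1.25k | Type I error at mean 1.25 | Variance of log rate ratio | Valid power, 50 per arm |
|---|---|---|---|---|
| 0.25 | 1.3125 | 8.7% | 2.9/50 = 0.058 | 82% |
| 0.5 | 1.625 | 12.4% | 3.4/50 = 0.068 | 76% |
| 1 | 2.25 | 19% | 4.4/50 = 0.088 | 65% |

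Example at k = 0.5: 1.960/sqrt(1.625) = 1.538, giving 2 × 0.062 = 12.4%. Power is Phi(0.6931/0.2608 − 1.960) = Phi(0.698) = 76%.

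The inflation depends on k times the mean. With both arms at 0.625 it is smaller: 8.7% at k = 0.5 and 12.4% at k = 1.

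**Step 5: simulation check** (gamma-Poisson counts, 50 per arm, 100,000 trials, no age term).

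| k | Type I, plain Poisson | Type I, robust variance | Type I, scaled variance | Power, robust | Power, scaled |
|---|---|---|---|---|---|
| 0 | 4.8% | 5.1% | 5.1% | 90.0% | 90.0% |
| 0.2 | 7.8% | 5.3% | 5.2% | 84.6% | 84.4% |
| 0.5 | 12.2% | 5.5% | 5.2% | 77.1% | 76.5% |
| 1.0 | 18.7% | 5.7% | 5.2% | 66.1% | 64.6% |

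The formulas hold up, and either adjusted variance brings the level back close to 5%. At k = 0 plain Poisson has 90.2% power, so the adjustment costs almost nothing when it is not needed.

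**Step 6: allow for drop-outs' data.** The intention-to-treat analysis includes everyone randomised. As an upper bound, take about 62 per arm, all fully followed:
- k = 0.2: variance 2.8/62 = 0.0452. Power = Phi(0.6931/0.2125 − 1.960) = about 90%.
- k = 0.5: variance 3.4/62 = 0.0548. Power = Phi(0.6931/0.2342 − 1.960) = about 84%.

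**The case against.** The strongest reply is that this is a condensed article. It names a model family, not a variance estimator. Poisson regression with a robust or scaled variance is still Poisson regression, and an unseen analysis plan may specify it. That stands, and it is why the type I error statement is conditional on model-based standard errors. It does not remove the point: the article names the method for its one primary test and sizes the trial on the same assumption, and a small change of wording would settle the matter.

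A second reply is that the design limits heterogeneity. It excludes chronic Pseudomonas and maintenance antibiotics, requires stability through a run-in, partly standardises antibiotic treatment and adjusts for age. These measures reduce variation between persons; nothing in the article shows that they remove it. Equally, nothing in the article supports any particular k, so the 19% and 65% at k = 1 are the far end of an assumed range and not a forecast.

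A reader might infer three stronger things that the article does not support:
- That the 90% was miscalculated. It was not; it reproduces, and the Sample size section states the Poisson condition openly.
- That 90% power is available only if dispersion is exactly zero. The intention-to-treat analysis takes all 125 randomised and all available data from drop-outs, so 90% could survive k of about 0.2 if follow-up were nearly complete.
- That the primary test is certain to be invalid. This depends on the variance estimator actually used and on the dispersion actually present.

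It is also fair to say that changing the model repairs the type I error but does not restore lost power.

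**Conclusion.** The point holds in conditional form. As named, the primary analysis does not allow for extra-Poisson variation, in a population that the article itself describes as varied. If model-based standard errors are used and some between-person variation is left unexplained by age, the error has a known direction: the interval is too narrow and the type I error is above 5%. Its size depends on k, which the article does not give. At a mean of 1.25 events it is about 8.7%, 12.4% and 19% for k = 0.25, 0.5 and 1.

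The stated power is right on its own terms but sensitive to them. With the planned 50 completers per arm, a valid test has about 82%, 76% and 65% power at those values. Data from drop-outs would raise this somewhat, to at most the Step 6 bounds. More data from drop-outs would not correct the type I error.

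**What to change.** Before unblinding:

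1. In Statistical analysis, name the primary model as negative binomial regression with a log link and age adjustment, or keep Poisson regression and state that a robust (sandwich) or scaled variance will be used. If the analysis plan already says so, carry that wording across.
2. In Sample size, replace the single 90% with the power over a plausible, justified range of dispersion, keeping 90% as the value for variance equal to mean.

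The cost is slightly wider intervals and a less favourable stated power. No patients or data collection are added.

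The change protects the 5% level and makes the power statement candid, but it does not restore 90%. By the log-rate formula, n per arm = 10.507 × (2.4 + 2k)/0.4805, that would take 64, 75 and 97 completers per arm at k = 0.25, 0.5 and 1, or 160, 188 and 243 enrolled at 20% dropout. The same formula gives 53 per arm at k = 0, so it is slightly stricter than the plan's own calculation. Table 1 of the article estimates 140 eligible patients in total, so stating the power honestly is the realistic course.

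### The mixed model for continuous secondary outcomes does not say how baseline enters or which contrast is tested, so it does not secure the change-based powers of 70% (FEV1) and 88% (LCI)

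*Protocol article*

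**What the plan says.** Under Statistical analysis, the continuous secondary outcomes are to be "modelled using a linear mixed model including a fixed time-specific treatment effect and random effects of trial site and person". The article adds that further confounders can enter as fixed main effects and gives age as its example. A baseline value is neither named nor ruled out. The section does not say whether a pre-treatment visit counts among the repeated outcomes, or which visit or contrast carries the treatment comparison.

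Under Sample size, the secondary powers refer to a difference "between treatments in the pre- to post-intervention change in" the outcome. For FEV1 the stated power is 70% for a 5-point difference, with an SD of change of 10%. For LCI it is 88% for a 5-point difference, with an SD of change of 8%. The basis is "a sample size of 100 participants completing the trial will be required, with 50 participants in each treatment arm". On the test itself, the section adds: "Calculations of power are based on two-sided testing with an alpha level of 0.05".

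The schedule in Table 2 supplies the baseline data. Spirometry is done at screening (month 0) and randomisation (month 1). Plethysmography, nitrogen washout, audiometry and QOL-PCD are all done at randomisation, and treatment ends at the month-7 visit. For the primary outcome, the article already defines an FEV1 decline "relative to the average of FEV_1_% predicted at screening and randomization".

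**The concern.** The power statement and the model concern the same outcomes, but nothing ties them together. The power rests on change, whose SD excludes stable differences between persons. The model sentence lists a fixed effect, two random effects and optional covariates, and baseline is in none of these lists.

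A person random effect does not settle the matter. Suppose each visit has its own treatment effect and the data are complete. The month-7 treatment coefficient is then the difference between the arms' raw month-7 means, and its variance contains the full spread between persons. Contrasting month 7 with randomisation in the same model removes that spread. The sentence therefore covers analyses of quite different precision.

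At stake is whether the secondary comparisons on FEV1 and LCI have the power claimed for them. Under a level reading, a chance difference between the arms at randomisation would also pass straight into the estimate.

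**Working it through.** **Inputs from the article (Sample size):** n = 50 completers per arm; difference 5 points; SD of change 10 (FEV1) and 8 (LCI); two-sided alpha 0.05. Hence √(2/n) = √(2/50) = 0.2.

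**Assumptions, not in the article:** the SD of levels at a visit, taken as 15 to 25 points for FEV1 (15 to 30 for LCI on its percent scale) and read as spread between persons within a site; equal variance at all visits; and a random-intercept correlation structure. Normal approximation, Power = Φ(5 / SE − 1.96).

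**Step 1. Reproduce the stated powers (comparison of change).**
- FEV1: SE = 10 × 0.2 = 2; 5/2 = 2.5; Φ(0.54) = 70.5% (t-test 69.7%). Stated: 70%.
- LCI: SE = 8 × 0.2 = 1.6; 5/1.6 = 3.125; Φ(1.165) = 87.8% (t-test 87.2%). Stated: 88%.

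Both agree.

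**Step 2. Link the SD of change to the SD of levels.** SD_change² = 2 × SD² × (1 − ρ), so for FEV1 ρ = 1 − 100/(2 × SD²). This gives ρ = 0.778, 0.875 and 0.920 at SD 15, 20 and 25.

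**Step 3. FEV1 power for each reading of the month-7 comparison.**
- Level: SE = 0.2 × SD.
- Change from randomisation: SE = 2, whatever the SD of levels.
- One baseline value as covariate: SE = 0.2 × SD × √(1 − ρ²).
- Mean of screening and randomisation as covariate: SE = 0.2 × SD × √(1 − R²), with R² = 2ρ²/(1 + ρ), if visit-to-visit variation is independent.

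| FEV1 analysis at month 7 | SD 15 | SD 20 | SD 25 |
|---|---|---|---|
| Difference in levels | 38.5% | 23.9% | 16.9% |
| Month 7 minus randomisation | 70.5% | 70.5% | 70.5% |
| One baseline as covariate | 75.5% | 73.3% | 72.3% |
| Mean of two baselines as covariate | 83.9% | 83.1% | 82.8% |

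Example at SD 20. Level: 5/4 − 1.96 = −0.71, power 23.9%. One baseline: residual SD 20 × √(1 − 0.766) = 9.68, SE 1.94, 5/1.94 − 1.96 = 0.62, power 73.3%.

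A generalised least squares calculation, with randomisation and three later visits as outcomes, gave the same figures for the level and change contrasts. Constraining the arms to be equal at randomisation gave the same figures as one baseline covariate.

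**Step 4. Sensitivity to the assumed SD.** At a level SD of 10 (ρ = 0.5) the level comparison also has 70.5% power, so nothing is lost; at 12 it has 55%. With one baseline covariate, power at these SDs is 82% and 79%.

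**Step 5. LCI.** At level SDs of 15 to 30, the level comparison has 38% to 13% power, the change contrast 87.8% throughout, and adjustment for one baseline 90% to 88%. At a level SD of 8 the level comparison again loses nothing.

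**Step 6. Chance imbalance.** The standard error of the baseline FEV1 difference between the arms is 0.2 × SD: 3, 4 and 5 points at SD 15, 20 and 25, against a target effect of 5 points.

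**The case against.** The strongest reply is that the article never proposes a raw comparison of month-7 levels. The only quantity it states for these outcomes is change. A model with a person effect and a time-specific treatment effect is also the usual form of a longitudinal analysis in which randomisation is one of the outcome visits. Read that way, the same model delivers the stated powers, as Step 3 shows. Age is only an example of a further covariate, and nothing excludes baseline. The full protocol or the analysis plan, neither of which is shown, may settle the point.

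Most of this stands. A reader might infer that the model fails to adjust for baseline and that the secondary analyses therefore have only 17–38% power for FEV1. The documents do not support that inference. It needs a contrast the article does not name and an SD it does not give. Nor would chance imbalance be bias: randomisation keeps the estimate unbiased, and the imbalance is reflected in the standard error. Using the mean of two FEV1 values to define an exacerbation creates no duty to use it in the secondary model.

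What the reply does not remove is that the article states both a change-based power and a model without tying one to the other. Adjusting for a baseline already collected is also more precise than either reading of the sentence, so the request does not depend on which reading was intended.

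**Conclusion.** The concern holds as an unresolved link between model and power, together with an improvement that costs almost nothing. It is not a demonstrated loss of power. The stated 70% and 88% are arithmetically right for change and are achieved if month 7 minus baseline is the tested contrast. Under a level reading, FEV1 power would be about 38% to 17%, conditional on assumed level SDs of 15 to 25 points.

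Against the change contrast, the gain from one baseline value is modest for FEV1: from 70.5% to about 72–76%. With the mean of the two pre-treatment values it is larger, to about 83%, if visit-to-visit variation is independent. Only secondary outcomes are affected.

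**What to change.** State in the model description that each outcome's baseline value is a fixed covariate. Alternatively, state that the randomisation visit is an outcome with the arms constrained to be equal there. Add visit and treatment-by-visit effects, and name the month-7 treatment contrast as the one tested. Using the mean of the screening and randomisation values as the FEV1 baseline is an optional refinement. If the full protocol or analysis plan already says this, a cross-reference is enough.

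The cost is one or two sentences of model wording, fixed before unblinding. The baseline measurements are already scheduled, so no visit, test or participant is added.
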